### Randomisation and blinding

Study enrolment will be implemented at a single convalescent hospital in Japan. Permuted block randomisation will be used, with a computerised random allocation sequence generated by an independent researcher throughout the study to facilitate data management. Randomisation is stratified by the ability or inability to walk independently. An answer form will be sent to the investigators, including a randomisation number.

Allocation results are disclosed to trial participants, outcome assessors and medical staff. Allocation results are not disclosed to the data analyst. To ensure that the statistical analysis is blind, the data analyst’s intervention/control group codes are masked until the data analysis is complete.

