### Trial design

This study is a single-centre, prospective, open-label, randomised controlled trial. An independent researcher not involved in enrolment or outcome measurements performed randomisation using a computer-generated 1:1 allocation sequence and permuted block size of 4. The flow chart of the present study is shown in figure 1.

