### Primary outcome

The primary outcome of the present study is to examine the safety and feasibility of the multidisciplinary intervention. Outside of rehabilitation, we track and record all adverse events, such as falls, trauma requiring treatment, and neurological deterioration. An independent assessor (MN) will assess the number of adverse events during the intervention. To examine the feasibility of the multidisciplinary intervention, we will assess the retention rate (wearing the device during the intervention period) and the completion rate of the intervention. In addition, we will confirm the percentage of participants who meet the eligibility criteria throughout the study.

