### Secondary outcomes

Secondary outcomes that are evaluated as exploratory are as follows:

Physical activity.Difference in changes in walking speed between the baseline and after the intervention.Difference in changes in Short Physical Performance Battery (SPPB) between the baseline and after the intervention.Six-minute walking distance (6MWD).Difference in changes in Functional Independence Measure motor function (FIM-M) between the baseline and after the intervention.Differences in SEPA changes between the baseline and after the intervention.

We define physical activity as the number of steps taken during the last 7 consecutive days of the intervention period, which is planned to take 4 weeks. Even if patients are discharged within 4 weeks, we will use the number of steps taken in the last 7 days as the outcome for both the intervention and control groups as long as the patient has been wearing the accelerometer for at least 2 weeks. Physical activity is not blinded to the assessors because the accelerometer’s data synchronises with the multiperson monitor.

A baseline assessment is performed within 1 week of admission. Patients who can walk and become eligible for the study sometime after hospitalisation will undergo a baseline assessment on enrolment. A physical therapist will assess physical function, FIM-M, and SEPA. Comfortable walking speed is measured at 10 m along a 16-m walkway. A walking aid may be used if necessary at the time of the measurement. SPPB is an objective tool for evaluating lower extremity physical function.^24^ 6MWD is a submaximal exercise test used to assess functional capacity that will be performed according to the American Thoracic Society guidelines in a 30-m long straight corridor under the guidance of a physical therapist.^25^ Patients are allowed to use their usual assistive devices, and intermittent assistance for fall prevention will be provided as necessary.

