Physical activity in patients with stroke may be affected by their level of self-efficacy.^9 10 14 31 32^ In the present study, multidisciplinary staff will encourage walking outside of rehabilitation for patients with high walking function and self-efficacy and actively provide opportunities for walking and other physical activities outside of rehabilitation for patients with lower walking function and self-efficacy. Although self-efficacy differs among patients, self-efficacy is expected to improve with goal achievements or increased walking opportunities, resulting in increased physical activity.

The present study has some limitations. Since this is a randomised pilot study, it will only be conducted at a single centre in Japan. Therefore, caution needs to be applied to the results’ generalisability. Furthermore, since the present study implements a multidisciplinary intervention, much medical staff will know which group the patients are allocated to. This may result in bias. Although we include patients who had a stroke who can walk 50 m, the accelerometers used in this study have not yet been reported to be reliable for patients who had a stroke. In the present study, multidisciplinary staff encourage and provide opportunities to promote physical activity outside of rehabilitation; however, it is impossible to ascertain the extent to which they comply and how often the intervention is implemented. Therefore, we may not always be able to standardise and ensure the fidelity of our interventions.

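### Allocation is disclosed to outcome assessors without exception, though the only reason given covers step counts; the independent adverse-event assessor, at least, could classify events without it

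*Protocol article*

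**What the plan says.** The Trial design section declares the trial open: "This study is a single-centre, prospective, open-label, randomised controlled trial". Randomisation and blinding then states who knows the arm: "Allocation results are disclosed to trial participants, outcome assessors and medical staff". It names one masked party: "Allocation results are not disclosed to the data analyst".

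The primary outcome is safety and feasibility. On safety, the Primary outcome section says "Outside of rehabilitation, we track and record all adverse events, such as falls, trauma requiring treatment, and neurological deterioration", and adds that an independent assessor "will assess the number of adverse events during the intervention". It does not say whether this assessor is masked. On feasibility, "we will assess the retention rate (wearing the device during the intervention period) and the completion rate of the intervention".

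Under Secondary outcomes, which are labelled exploratory, "A physical therapist will assess physical function, FIM-M, and SEPA". That section explains why assessors of physical activity are not blinded: the accelerometer data synchronise with the shared monitor. It gives no such explanation for the other outcomes. It adds that physical or occupational therapists score FIM as part of the hospital's rehabilitation protocol.

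The Discussion describes the physical therapist as the main facilitator of the intervention. Among the limitations, it says that many medical staff will know the allocation, and concludes: "This may result in bias".

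**The concern.** An open design explains why patients and treating staff know the arm. It does not by itself explain why people who classify events or score tests should be told. The protocol makes that disclosure expressly, so this is a stated choice and not a detail lost when the article was condensed.

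Two kinds of outcome are exposed. Some adverse-event categories, such as neurological deterioration or whether trauma needed treatment, call for judgement, and they belong to the primary outcome. Walking speed, SPPB, 6MWD and FIM-M depend on a tester or rater. For 6MWD the tester may give intermittent help to prevent falls, and Table 1 shows no baseline value against which a tester effect could be judged.

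The trial is meant to supply preliminary data for a larger efficacy study. Differences that arise from knowledge of the arm would carry over into the planning of that study.

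**Working it through.** **1. Who is told, and why.**

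| Outcome | Who assesses it | Reason given for disclosure | Dependence on assessor |
|---|---|---|---|
| Adverse events: classification and count | Independent assessor | None | Some; low for falls, higher for neurological deterioration |
| Adverse events: first capture | Ward and study staff | Open design | Staff are unmasked in any case |
| Retention, completion | Device wear and delivery of the intervention | Not needed | Little |
| Steps | Accelerometer | Monitor synchronisation | Little |
| Walking speed, SPPB, 6MWD | Physical therapist | None | Material |
| FIM-M | Physical or occupational therapist, in routine care | None | Material |
| SEPA | Patient's own report | Open design | The patient is unmasked in any case |

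The only specific reason for unmasked assessment is attached to the outcome that needs masking least. The outcomes for which masking could help are the classification of adverse events and the four therapist-assessed measures.

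**2. Does the disclosure reach the adverse-event assessor?** The disclosure sentence is general and has no exception. The Primary outcome section calls the assessor independent and is silent on masking. Read together, the wording includes this person, but only by inference. Either the assessor is told, which weakens the value of independence, or the two sections do not fit together. Both cases need a change of text.

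**3. Scale.** The plan states no figure to reproduce on this point, and masking would not alter the target of 32. The figures below are orientation only. They assume equal arms, 32/2 = 16 patients each.

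- *Adverse events as patients affected.* One patient reclassified changes an arm's proportion by 1/16 = 6.25 percentage points. The protocol speaks of the number of events, so this applies only if results are also summarised per patient.
- *A rated outcome with no true effect.* Let knowledge of the arm shift ratings by b SD (assumed). The standard error of the difference in SD units is √(2/16) = 0.354. The chance of two-sided p<0.05 is Φ(b/0.354 − 1.96) + Φ(−b/0.354 − 1.96). The protocol does not say whether its tests are two-sided.

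| Assumed shift b (SD) | Chance of p<0.05 |
|---|---|
| 0 | 5% |
| 0.1 | 5.9% |
| 0.2 | 8.7% |
| 0.3 | 13.6% |
| 0.5 | 29.3% |

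**4. What masking cannot repair.** Suppose 10% to 30% of patients have an event (assumed). The expected number per arm is 16 × 0.10 = 1.6 to 16 × 0.30 = 4.8. If one arm captured only 75% or 50% of these, the loss would run from 1.6 × 0.25 = 0.4 to 4.8 × 0.50 = 2.4. That loss occurs on the ward, before any assessor sees a record.

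**The case against.** The strongest reply is that the trial is openly declared as open-label, says plainly who is masked, and already admits possible bias from staff knowing the allocation. Physical therapists are listed among the medical staff under Outcome measures, so that admission arguably reaches the functional raters. The secondary outcomes are exploratory, in a pilot without a power calculation. Feasibility needs little judgement. Falls, the first adverse event listed, need little adjudication. Goals and monitor data are shared among staff at a single site, so a rater from the same team would often learn the arm anyway.

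Most of this stands, and it lowers the weight of the point. It does not explain telling an assessor described as independent, whom the Discussion's limitation does not mention.

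A reader might also infer four stronger things that the documents do not support:

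- *That the adverse-event assessor is known to be unmasked.* This follows only from the general disclosure sentence; the Primary outcome section does not say so.
- *That existing staff could remove the bias.* The protocol mentions more than one therapist, for eligibility checks and for FIM scoring, but gives no rota or pool of uninvolved raters. Unmasked staff would still capture events.
- *That the therapist who sets a patient's goals also tests that patient.* The protocol says only that a physical therapist does the tests. The roles are not separated, but neither are they stated to be the same person's.
- *That the bias favours the intervention.* Closer staff contact in that arm could equally raise the detection of events.

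**Conclusion.** The point holds in a limited form. The protocol discloses allocation to all outcome assessors, gives a reason for step counts only, and leaves the masking of the independent adverse-event assessor to inference. Masking that assessor when events are classified is a cheap improvement to a primary outcome, because the person is already in place. Masking the week-4 raters is desirable where it can be arranged, but depends on staffing that the documents do not describe.

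The size of any bias cannot be derived from the documents. The 6.25 points per patient rest on 16 per arm and a per-patient summary; the 5.9% to 29.3% rest on assumed shifts of 0.1 to 0.5 SD. No figure in the protocol is wrong, and the sample size is unaffected. The gain is less bias in classification and rating. Event capture by unmasked staff and self-reported SEPA would remain exposed, and steps, retention and completion would change little.

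**What to change.** 1. In Randomisation and blinding, take outcome assessors out of the blanket disclosure. Keep the step-count exception, with its reason, under Secondary outcomes.
2. In Primary outcome, state that the existing independent assessor classifies adverse events in both arms from descriptions with allocation and intervention details redacted.
3. Under Secondary outcomes, state that week-4 walking speed, SPPB, 6MWD and FIM-M are assessed by someone who does not treat the patient and is not told the arm, where existing staffing allows. Record each instance of unmasking.
4. Where item 3 cannot be met, name assessor knowledge of allocation explicitly among the limitations in the Discussion.

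The cost is redaction of event notes and some scheduling. FIM-M is the hardest of the four measures, because it is scored in routine care. Some residual unmasking on a single ward should be expected and reported.

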### Outcome measures

After enrolment, all patients wear an accelerometer on their waist belt 24 hours/day, except when bathing or changing clothes. We will use the average daily number of steps taken as an index of daily hospitalised physical activity. This will be measured by a UW-204NFC (A&D Company, Tokyo, Japan) three-dimensional accelerometer that calculates steps, total calories, calories burned and distance. Patients will wear the accelerometer for a minimum of 2 weeks and a maximum of 4 weeks.

Daily hospitalised physical activity is sent to the multiperson physical activity monitoring system (MEDICA Cloud, Funabashi, Japan) through an offline connection. Medical staff, including a physician, nurse and physical therapist, will check physical activity through the monitor (figure 2). This multiperson monitor allows medical staff to observe not only a patient’s daily physical activity level but also provides a visual graph showing the degree of an increase or decrease from the previous week, a percentage breakdown of steps taken during the week, and the average walking speed when wearing the accelerometer (figure 3).

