### Eligibility criteria

The inclusion and exclusion criteria for the present study are shown in box 1. Two or more physical therapists or physicians will assess patients’ eligibility to participate in the present study. We will include patients hospitalised for stroke with the ability to walk 50 m with at least hand assistance, regardless of the use of braces or walking aids, and aged ≥20 years. If a patient does not meet the above criteria at the time of admission, they will still be included in the present study if they can walk during hospitalisation. All patients will obtain informed consent before inclusion and randomisation (table 1).

Box 1Inclusion and exclusion criteria of the present studyInclusion criteriaPatients hospitalised for strokePatients with the ability to walk 50 m with at least hand assistanceAge≥20 yearsExclusion criteriaSAHStroke after cardiovascular surgeryPremorbid mRS≥3Cognitive impairment (MMSE score<21)^33^Patients who are expected to be hospitalised for less than 2 weeksPatients who have neurological, orthopaedic, or medical diseases other than stroke that seriously affect physical activityPatients who cannot give consent for research participation.MMSE, Mini-Mental State Examination; mRS, modified Rankin Scale; SAH, subarachnoid haemorrhage.

**Table 1 T1:** Summary of the study schedule

Time point	Study period			
	Baseline	Allocation	Intervention	
			Week 1	Week 4
Enrolment				
Demographic data	×			
Informed consent	×			
Allocation		×		
Interventions				
Intervention group				
Conventional rehabilitation	×		×	×
Multidisciplinary intervention			×	×
Self-monitoring of PA			×	×
Control group				
Conventional rehabilitation	×		×	×
Assessment				
Stroke severity				
NIHSS	×			
Motor dysfunction				
FMA-LE	×			
Safety			×	×
Feasibility	×		×	×
PA			×	×
Physical function				
Walking speed	×			×
SPPB	×			×
6MWD				×
Functional outcome				
FIM-M	×			×
Self-efficacy for PA	×			×

FIM-M, Functional Independence Measure for motor function; FMA-LE, Fugl-Meyer Assessment for lower extremity; 6MWD, 6-minute walking distance; NIHSS, National Institutes of Health Stroke Scale; PA, physical activity; SPPB, Short Physical Performance Battery.

The present study was registered at the University Hospital Medical Information Network Clinical Trial Registration before the enrolment of patients (ID: UMIN000046731). A flow chart of participants will be reported according to the Consolidated Standards of Reporting Trials guidelines (figure 1).

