#### Intervention group

An overview of the interventions is shown in figure 4. We will instruct patients in the intervention group to self-monitor their hospitalised physical activity. Specifically, we plan to use the method to self-monitor physical activity previously described by Kanai *et al* and Atkins *et al*.^16 19^ Patients in the intervention group will be asked by the physical therapist to record physical activity measured with the accelerometer on an exercise calendar at the end of the day. The patient and physical therapist collaboratively set a target number of steps per day, considering the patient’s walking ability and prestroke physical activity. By sharing these physical activity goals with multidisciplinary staff, we will encourage patients to promote physical activity outside rehabilitation. The standardised wording used by multidisciplinary staff to instruct patients is ‘try to walk more than you did last week’ and ‘keep self-monitoring your steps’. The physical therapist will provide visual feedback on changes in the number of steps taken over time and goal achievement to the patient every 7 days after study enrolment using the multiperson monitor. The physical therapist praises the patient if the patient achieves the physical activity target. If the patient does not achieve the physical activity target, the physical therapist will discuss a modified physical activity target with the patient by viewing the multiperson monitor display. With the instructions for self-monitoring physical activity and the multidisciplinary intervention, patients will be expected to improve their self-efficacy for physical activity (SEPA) and adopt other positive health behaviours.

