### Statistical analysis and sample size

We will perform intention-to-treat analyses. Results will be expressed as the mean±SE of the mean or the mean±SD for normally distributed data and as a median (25th–75th percentiles) for non-normally distributed data. The number of steps taken will be examined by an analysis of covariance (ANCOVA) with adjustments for baseline age, sex, NIHSS and FMA-LE. Other outcomes will be analysed by ANCOVA, an unpaired *t*-test, or the Mann-Whitney U test for continuous variables, and the χ^2^ test or Fisher’s exact test for categorical variables. A p value of <0.05 will be considered to indicate significance in all tests.

Since this is a pilot study, a formal power calculation was not performed. Based on the effect sizes of our previous studies on physical activity after stroke, one of the secondary outcomes, we will use a target sample size of 32 subjects as a guide.

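### Daily steps are not recorded before allocation, so the exploratory step comparison gives up precision and cannot directly check or adjust for starting activity (minor)

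*Protocol article*

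**What the plan says.** Outcome measures (protocol article) starts step recording at entry: "After enrolment, all patients wear an accelerometer on their waist belt 24 hours/day, except when bathing or changing clothes". It then limits the period: "Patients will wear the accelerometer for a minimum of 2 weeks and a maximum of 4 weeks".

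Table 1, "Summary of the study schedule", under Eligibility criteria, marks physical activity at Week 1 and Week 4 and leaves Baseline and Allocation blank. Walking speed, SPPB, FIM-M and self-efficacy are each marked at Baseline and Week 4. The multidisciplinary intervention and self-monitoring are both marked at Week 1.

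Secondary outcomes gives the step endpoint: "We define physical activity as the number of steps taken during the last 7 consecutive days of the intervention period, which is planned to take" (the sentence closes by giving the length as four weeks). The same section says "A baseline assessment is performed within 1 week of admission". Patients who become eligible later in their stay are assessed on enrolment.

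Under Intervention group, the therapist gives visual feedback "on changes in the number of steps taken over time and goal achievement to the patient every 7 days after study enrolment".

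Statistical analysis and sample size sets the model: "The number of steps taken will be examined by an analysis of covariance (ANCOVA) with adjustments for baseline age, sex, NIHSS and FMA-LE". It names physical activity as the outcome whose earlier effect sizes guided the target of 32.

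**The concern.** The trial's hypothesis, in the Introduction and again in the Discussion, is that the intervention promotes physical activity, and steps are its measure. Four of the six secondary outcomes are defined as changes from baseline. Steps can only be a level reached after allocation. They are read repeatedly, but the first planned reading comes after treatment has begun. (The 6-minute walk also has no baseline mark, but it is scheduled once only.)

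Starting activity is likely to vary widely. Patients range from needing minimal assistance to full independence, some join only once they can walk, and some may become independent during the intervention. In a trial of 32, the arms could differ in starting activity by chance, and nobody could see that directly or adjust for it. This is a measurement not taken, so no later analysis plan could recover it.

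**Working it through.** **1. Is there really no step count before allocation?** The words after enrolment do not by themselves exclude brief wear before allocation. Three other statements, read together, leave no place for it:
- Table 1 leaves the Baseline and Allocation cells for physical activity blank.
- The maximum wear of 4 weeks equals the planned intervention of 4 weeks.
- The 7-day feedback cycle counts from enrolment.

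No section describes a run-in.

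**2. Can Week 1 serve as a baseline?** No. Self-monitoring and the multidisciplinary intervention are marked as running in Week 1, and staff are told to say "try to walk more than you did last week". Week 1 steps may already carry part of the treatment effect, and adjusting for them could remove it. The protocol does not propose this use; the point is only that Week 1 does not fill the gap.

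**3. The plan's own figure.** The target of 32 cannot be reproduced, because no effect size, SD or power is given. Working backwards with 16 per arm, two-sided 5% (sidedness assumed) and 80% power, the detectable difference is (1.960 + 0.842) × √(2/16) = 0.99 SD by the normal approximation.

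**4. Chance imbalance in starting steps.** With 16 per arm, the standard error of the difference in means is √(2/16) = 0.354 SD. For a gap above 0.5 SD in either direction, z = 0.5/0.354 = 1.414 and the probability is 0.157, about 16%. This ignores the stratification by walking independence, so the true figure is lower. A 0.5 SD gap would carry 0.5 × r SD into the final comparison: 0.15, 0.25 or 0.35 SD at r = 0.3, 0.5 or 0.7.

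**5. Precision gained by measuring it.** Let r be the correlation of starting with final steps, given the covariates already in the model. The documents give no value, so r is an assumption. The standard error is multiplied by √(1 − r²), and the equivalent gain in sample size is 1/(1 − r²).

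| r (assumed) | √(1 − r²) | Cut in SE | 1/(1 − r²) | Detectable difference, 80% power |
|---|---|---|---|---|
| 0.3 | 0.954 | 5% | 1.10 | 0.95 SD |
| 0.5 | 0.866 | 13% | 1.33 | 0.86 SD |
| 0.7 | 0.714 | 29% | 1.96 | 0.71 SD |

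The last column is 0.99 SD times the second. The one degree of freedom spent on the extra covariate is ignored.

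**The case against.** A reader might infer more than the documents support.

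- *That the step comparison is biased or cannot show an effect.* It is a randomised comparison of final levels and is unbiased on average without a baseline. A rise within one arm would prove little in recovering patients anyway.
- *That the pilot cannot supply within-patient variability for a larger trial.* Controls wear the device for 2 to 4 weeks, receive no self-monitoring instruction and do not see their counts. Their data give day-to-day variability and week-to-week correlation, though only after allocation and from about 16 patients.
- *That the first step target has no reference.* Intervention group bases it on walking ability and activity before the stroke, and the first feedback follows a recorded week.

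The design also softens the problem. Randomisation is stratified by walking independence, the model adjusts for NIHSS and FMA-LE, and baseline walking speed, SPPB and FIM-M would show an imbalance in walking capacity. These reduce the 16% figure. They do not replace a count of what patients actually do on the ward.

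The precision gain depends on a correlation that no section supports. Changing activity over about four weeks argues for the lower end, where the gain is small. Finally, steps are an exploratory secondary outcome in a pilot with no formal power calculation. That objection stands, and it sets the severity.

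**Conclusion.** The point holds as a minor one. The schedule fixes the first step reading after allocation, so chance imbalance in starting activity cannot be seen or adjusted for directly, and no change from before treatment can be reported. The lost precision is worth about 10%, 33% or 96% more patients at an assumed r of 0.3, 0.5 or 0.7. A starting gap above 0.5 SD would arise in about 16% of randomisations without stratification, and in fewer with it. Validity of the randomised comparison is not in question, and the primary safety and feasibility outcomes are untouched.

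**What to change.** Have patients wear the existing accelerometer for a few days between consent and allocation, within the current baseline window where possible, with counts hidden from patients in both arms. Then:
- mark physical activity at Baseline in Table 1;
- add mean daily steps before allocation to the step ANCOVA;
- count the wear limits in Outcome measures and the 7-day feedback cycle in Intervention group from allocation.

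The device and monitoring system are already in use, and control patients' counts are already hidden from them. The cost is a delay of a few days to allocation. Patients who become eligible after admission have no existing window to absorb it. For short stays, exposure is slightly shortened, and because only an expected stay under 2 weeks is excluded, a few patients may fall short of the 2 weeks of wear that the step outcome requires. Staff may also see the counts on the monitor during the run-in.

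If this is not feasible, state that only final step levels are compared, and adjust for baseline walking speed and the walking-independence stratum, both already collected. Do not use Week 1 steps as a baseline covariate.
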